### Study sites

The study will be conducted at Mildmay Uganda, an NGO with headquarters in Uganda’s capital, Kampala. Mildmay Uganda specializes in the provision of comprehensive HIV and AIDS prevention, care, and treatment services. Mildmay Uganda provides quality outpatient and inpatient HIV care and trains health care workers throughout Uganda and the region in the provision of such care. Mildmay serves over 105,000 patients (15,000 at the main site in Lweza and over 95,000 at supported health facilities in 8 districts in Central Region of Uganda). The main-site facility has a well-trained, experienced team of clinicians and health workers, and modern laboratory infrastructure with ability to do virology and other tests. The Mildmay Uganda laboratory is accredited by the South African National Accreditation System (SANAS) for International Organization for Standardization (ISO) 15,189:2012 for medical laboratories and also acts as a national back up laboratory for the government of Uganda Central Public Health Laboratories. Some of the services provided include the following: HIV counseling and testing; pediatric and adult HIV prevention, treatment and care services; sexual and reproductive health services; diagnostic (laboratory) services and radiology; rehabilitative services (nutrition, physiotherapy, occupational therapy); safe male circumcision (SMC); ophthalmic; and dental care. Of the 15,000 patients served at the main site in Lweza, 11% are children below 18 years, 65% are female, and 100% of all clients in care are on ART. Mildmay is one of a growing number of facilities with a well-established electronic medical records system in Uganda.

### Sampling and participants

We expect to enroll 1256 individuals for the observation phase of the study that serves to measure baseline adherence. Monitoring baseline adherence will ensure that individuals being randomized to the interventions are indeed those in need of adherence support, i.e., have relatively low baseline mean adherence of less than 90%.

We arrived at this starting sample size in the following way. For the primary outcome of adherence, a sample size of 140 participants in each arm (*n* = 560 total) will be able to detect an 8 percentage point (pp) difference in mean adherence between each treatment arm and control, and compared to each other. The corresponding difference at month 24 is 9 pp. This assumes mean control group adherence of 62%. In order to reach this required sample size at year 3, we assume 6% attrition per year over 2 years of the study (1.06^2 = 1.1236) which results in a sample size for the beginning of GOALS recruitment to be 629 (560 × 1.1236). To ensure an even number across the four study arms, we reduce this target from 629 to 628. We then assume that 50% of those who complete the adherence observation phase are eligible for the GOALS intervention. We therefore need a starting sample size of 1256 ((628/50) × 100). All assumptions surrounding attrition rates and rates of adherence are based on data from PI [name]’s previous study at the same site.

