### Sample size and power

We have calculated the size of effects that our sample will be able to detect with 80% power (2-tailed test) with regard to outcomes at months 12 and 24, and assuming 10% attrition every year (we observed 8% attrition for our pilot study, so this is a conservative estimate). For the *primary outcome of adherence*, a sample size of 140 participants in each arm (*n* = 560 total) will be able to detect an 8-percentage point (pp) difference in mean adherence between each treatment arm and control, and compared to each other. The corresponding difference at month 24 is 9 pp. This assumes mean control group adherence of 62%, based on our pilot data. For the *secondary outcome of viral suppression*, we use a conservative estimate of about 70% of clients in the control group showing suppression based on discussions with the Mildmay team. Our sample size of 140 participants in each of the three arms will be able to detect about a 10 pp difference at month 12, and 11 pp at month 24. These represent conservative estimates of minimum detectable effect size that do not account for stratified randomization that we will perform to increase power, and to achieve better balance compared to a simple random draw [39].

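### The 628 is derived from 6% yearly attrition over two years and the power statement from 10% a year; under neither rate do the stated 560 remain at year 3

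*Protocol article*

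**What the plan says.** Two sections of the Protocol article give the sample size reasoning.

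- **Sampling and participants.** The starting point is that "a sample size of 140 participants in each arm (*n* = 560 total) will be able to detect an 8 percentage point (pp) difference", with 9 pp at month 24. The 560 are then treated as the number that must be left: "In order to reach this required sample size at year 3, we assume 6% attrition per year over 2 years of the study". The factor is 1.06² = 1.1236, which gives 629, and "we reduce this target from 629 to 628" so that the arms are equal (157 each). Assuming half are eligible after the observation phase, 1256 are to be enrolled. The attrition rate is credited to a previous study at the same site.
- **Sample size and power.** The power is 80%, two-tailed, for months 12 and 24, "assuming 10% attrition every year (we observed 8% attrition for our pilot study, so this is a conservative estimate". The basis is again "a sample size of 140 participants in each arm", with the same 8 and 9 pp.

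On follow-up, the Abstract describes a 3-year trial, and Design collects electronic adherence for 24 months from the start of the intervention and for 12 months after it ends. Handling missing data and attrition says only that yearly attrition in earlier studies was well below 10%. Retention says that no outcome data are collected once a participant discontinues.

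**The concern.** One sample size rests on two yearly attrition rates, and the article does not say which one governs. The role of the 140 also shifts. In Sampling and participants it is what remains after attrition. In Sample size and power it looks like the number to which attrition is then applied, because with a fixed number and a fixed SD the detectable difference would not rise from 8 to 9 pp between months 12 and 24.

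The horizon is unclear as well. The target is placed at year 3, but only two years of loss are allowed for, while adherence is measured to month 36. The inflation also multiplies by 1.06² where retention calls for division by 0.94².

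At stake is the number of participants the trial can expect to have in the later phases. Because discontinuation ends outcome collection, attrition translates directly into missing primary-outcome data. A later report that cited 560 as the planned retained sample would be citing a number that the plan's own assumptions do not deliver.

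**Working it through.** **Inputs.** From Sampling and participants: 560 needed (140 per arm), 6% a year, two years, 628 randomised (157 per arm), 50% eligible. From Sample size and power: 10% a year, 80% power, two-tailed, 8 pp at month 12 and 9 pp at month 24. Not stated: alpha and the SD of mean adherence.

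**1. The plan's own figures.** 560 × 1.06² = 629.2, and 628 / 0.50 = 1256. Both reproduce.

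**2. Retained from 628.** Formula: 628 × (1 − d)^years.

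| Yearly attrition | Month 12 | Month 24 | Month 36 |
|---|---|---|---|
| 6%, total | 590 | 555 | 522 |
| 6%, per arm | 148 | 139 | 130 |
| 10%, total | 565 | 509 | 458 |
| 10%, per arm | 141 | 127 | 114 |

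Against 560, the shortfall at month 24 is 5 people at 6% (0.9%) and 51 at 10% (9%). At month 36 it is 38 (7%) and 102 (18%). Month 12 meets 560 at both rates.

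**3. Break-even.** 560 remain only if yearly attrition is at most 1 − (560/628)^(1/2) = 5.6% over two years, or 1 − (560/628)^(1/3) = 3.7% over three.

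**4. Number needed to keep 560.** Formula: 560 / (1 − d)^years.

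- 6%: 634 over two years, 675 over three.
- 10%: 692 over two years, 769 over three.

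Multiplying instead of dividing therefore costs 634 − 629 = 5 people at 6% over two years.

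**5. How 140 is used in the power statement.** Applying 10% a year to 140 gives 126 at month 12 and 113 at month 24. An exact 8.0 pp at 126 becomes 8.0 × √(126/113.4) = 8.4 pp at 113; with rounding at both ends, 8 and 9 pp are possible. Pairing 8 pp with 140 and 9 pp with 113 also fits, with implied SDs of 23.9 and 24.2 pp. Under both readings 140 is a number before attrition, unlike in Sampling and participants.

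**6. Detectable differences from 157 per arm.** Assume alpha 0.05 two-sided, so the multiplier is 1.96 + 0.84 = 2.80. The SD implied by 8 pp is 22.7 pp if 126 per arm are analysed at month 12 and 23.9 pp (about 24) if 140 are. Formula: 2.80 × SD × √(2/n), at 10% attrition.

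| | n per arm | Detectable difference | Stated |
|---|---|---|---|
| Month 12 | 141 | 7.6 to 8.0 pp | 8 pp |
| Month 24 | 127 | 8.0 to 8.4 pp | 9 pp |
| Month 36 | 114 | 8.4 to 8.9 pp | none |

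With SD 23.9 and 10% attrition, power at month 24 is about 85% for 9 pp and 76% for 8 pp; at month 36, power for 8 pp is about 72%.

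**The case against.** A reader might infer that the trial is underpowered, or that its stated detectable differences are too favourable. The documents do not support that. At month 12 more than 560 remain even at 10%. The recomputed month-24 difference is smaller than the stated 9 pp under the back-solved SD. No month-36 difference is claimed anywhere, so none can be wrong.

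Two parts of the criticism are small. The multiplication in place of division is worth five people. And if year 3 means its beginning, that is month 24, which fits the two years of attrition in the same sentence, then the 6% case falls short by only those five.

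A reader might also infer that 6% is wrong because the pilot showed 8%. The article does not say that the 8% is a yearly rate, nor that the pilot and the previous study behind the 6% are the same study. The remark in Handling missing data and attrition is compatible with either rate.

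Finally, the month-36 counts are not the exact planned contrast. The model uses weekly observations clustered by person, the persistence phase is analysed over all its months, and low adherers in the fixed-goal arm are moved after month 18. People lost during year 3 still contribute until they leave.

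All of this limits the consequence. It leaves standing that two rates support one number, that 140 has two meanings, and that 560 do not remain at year 3.

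**Conclusion.** The point holds as an inconsistency and a misstated retained sample, not as a power failure. The retention counts rest only on the article's own rates compounded yearly: 555 or 509 at month 24 and 522 or 458 at month 36, against 560. The material gaps are the 10% rate and, if year 3 extends to month 36, the third year of loss.

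The detectable differences depend on an assumed two-sided alpha of 0.05, an SD back-solved from a rounded 8 pp, and a constant SD over time. They indicate only that the stated 8 and 9 pp are not shown to be optimistic.

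**What to change.** - Use one yearly attrition rate and one time horizon in Sampling and participants and in Sample size and power, and say what the rate is based on.
- Say whether 140 per arm is a number before or after attrition, and at which month.
- Keep 628 (157 per arm) and drop the claim that 560 remain at year 3. The 628 still has a basis: at 10% it leaves 565 at month 12.
- State the expected numbers per arm at months 12, 24 and 36: about 141, 127 and 114 at 10%, or about 148, 139 and 130 at 6%.
- Restate the detectable differences from the sponsor's own SD and alpha, both shown. The ranges in the check above are placeholders until those are given.

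This costs wording only, with no change to design or recruitment. Keeping the claim of 560 instead would mean randomising 636 to 772 in equal arms and, at 50% eligibility, starting with 1272 to 1544, depending on rate and horizon. The stated power does not require this.

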#### Wisepill procedures

All participants will be given a Wisepill device upon recruitment into the observation period of the study. At the time they receive the device, they will be instructed in how to refill the pill box. The team will only monitor adherence to one antiretroviral as studies show that rates of adherence do not differ significantly across a patient’s medications.

Participants will be asked to use the Wisepill device continuously throughout the study and to notify the study coordinator if their provider changes their regimen during the study (which may be a real possibility, in particular for the youths on prophylaxis). They will be asked to remove only one dose at the time of ingestion and will also be informed that the data recorded will not be shared with clinicians. The team will carefully discuss the restrictions associated with the device with the patient and solutions to potential concerns that are acceptable to both the patient and the project will be generated. We will review the instructions and restrictions with the participant at each successive clinic visit.

The 3-month period will also allow individuals to incorporate the device into their daily life and to test and troubleshoot its use prior to beginning the intervention. During this time, we will monitor their adherence. Participants who are unable to use the device consistently will be excluded from the study after careful discussion of the reason for the low observed adherence with the patient (to avoid excluding participants with truly low adherence that is not related to an inability or unwillingness to use the Wisepill device). We will also exclude participants who have adherence above 90% during this period to target the intervention at those with low Wisepill-measured adherence (as those over 90% adherence have little room and/or need for improvement).

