### Limitations

This study has several limitations. First, the study will only include 640 patients in one clinic in Uganda. Although our sample size is well powered to detect clinically important effects, it is not clear that our results will extrapolate to other areas of Uganda or other countries. Second, although adherence is measured using Wisepill devices, which is currently one of the most accurate ways to measure adherence, we may not be able to exclude the possibility that some participants consciously manipulate the pill bottle openings to increase their chances of receiving the incentives. Third, while we conceptually test out different ways of structuring incentives, there is little guidance on the “right” size of incremental steps to effectively lead participants to clinically meaningful adherence levels, and further research is required to determine their most effective magnitude.

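### 1256 is derived as the number who must complete observation but is used as the number to enrol, and the randomised total appears as both 628 and 640

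*Protocol article*

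**What the plan says.** Sampling and participants in the protocol article sets out the whole chain.

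- The power calculation needs "a sample size of 140 participants in each arm", 560 in all.
- For follow-up losses, "we assume 6% attrition per year over 2 years of the study (1.06^2 = 1.1236"), which gives 629.
- The target is then rounded: "To ensure an even number across the four study arms, we reduce this target from 629 to 628".
- The eligibility step reads "We then assume that 50% of those who complete the adherence observation phase are eligible for the GOALS intervention".
- The conclusion follows directly: "We therefore need a starting sample size of 1256", computed as 628 divided by 50 and multiplied by 100.

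The same section opens by using that figure as an intake number: "We expect to enroll 1256 individuals for the observation phase of the study that serves to measure baseline adherence". The Recruitment section also treats 1256 as the number of clients to recruit, at the visit where the device is handed out.

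The article foresees departures between that visit and randomisation. Wisepill procedures says "Participants who are unable to use the device consistently will be excluded from the study", after discussion of the reason. Exclusion criteria removes people whose phone access lapses during the 3 months. Baseline survey and randomization depends on a return visit at about 3 months, for which some participants must be called back.

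On the randomised total, the Abstract and the derivation give 628 (157 per arm), while Limitations says "the study will only include 640 patients in one clinic in Uganda".

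**The concern.** The denominator of the 50% is people who finish observation. Dividing 628 by that rate gives a number of finishers, not of starters. The two are equal only if everyone enrolled completes about 3 months with the device. The only loss term in the chain, 1.06 squared, covers the two years from the start of the intervention phase, so nothing covers the observation phase.

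At stake is the number randomised. If 1256 is used as the intake figure and the 50% is right, any early loss takes the randomised number below 628, and the number left at the end falls further below 560. A second randomised total, 640, leaves the reader unsure which figure is the target.

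**Working it through.** **Inputs from the article.** 140 per arm and 560 in total; 6% attrition per year over 2 years, applied as a factor of 1.1236; 628 to randomise; 50% eligible among completers; 1256 to enrol (all Sampling and participants). 10% attrition per year; 8 pp detectable with 140 per arm at 80% power, two-tailed; 9 pp at month 24 (Sample size and power).

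**Assumptions.** L is the share of those enrolled who leave before completing observation. The article does not give it, so a range is shown. Two-sided alpha is taken as 0.05, because the article does not state it.

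**Step 1: reproduce the plan's figures.**
560 × 1.06² = 560 × 1.1236 = 629.2, taken as 629 and reduced to 628.
628 / 0.50 = 1256. The stated figure reproduces exactly, with no term for L.

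**Step 2: a range for L.** Scaling the article's annual attrition to 3 months:
1 − 0.94^(1/4) = 1.5%
1 − 0.90^(1/4) = 2.6%
Losses of 5% and 10% are added as illustrations.

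**Step 3: yield and starters needed.**
Randomised = 1256 × (1 − L) × 0.50
Left after follow-up = randomised / 1.1236 (the plan's own factor)
Starters needed for 628 = 1256 / (1 − L)

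| L | Randomised | Per arm | Left after follow-up | Starters needed |
|---|---|---|---|---|
| 0% | 628 | 157 | 559 | 1256 |
| 1.5% | 618 | 155 | 550 | 1276 |
| 2.6% | 612 | 153 | 544 | 1290 |
| 5% | 597 | 149 | 531 | 1323 |
| 10% | 565 | 141 | 503 | 1396 |

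The 559 at zero loss reflects only the rounding from 629 to 628. The loss at which the randomised number itself drops below 560 is 1 − 560/628 = 10.8%.

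**Step 4: effect on the detectable difference.**
SD implied by 8 pp at 140 per arm: 8 / (2.8016 × √(2/140)) = 23.9 pp.
Detectable difference = 2.8016 × 23.9 × √(2/n), with n the number left per arm.

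- L = 5%: n = 531/4 = 132.7, giving 8.2 pp; power for 8 pp is about 78%.
- L = 10%: n = 503/4 = 125.8, giving 8.4 pp; power for 8 pp is about 76%.
- L = 20%: n = 447/4 = 111.8, giving 8.95 pp; power for 8 pp is about 71%.

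All three lie within the 9 pp stated for month 24.

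**Step 5: the second total.** 640 − 628 = 12. No step in the derivation produces 640.

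**The case against.** A reader might infer that the trial falls short of 560 before follow-up begins, or that its stated detectable differences fail. The documents support neither. Every yield in the table before follow-up attrition (618, 612, 597, 565) exceeds 560, and an observation loss above 10.8% would be needed to change that. The stated month-24 difference is 9 pp, and even a 20% loss stays just inside it.

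A reader might also infer that enrolment stops at 1256. The article does not say so. It speaks of an expectation, allows extra recruitment time, and gives 628 in the Abstract as the number to be enrolled in the trial.

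Nor does the mismatch cover every loss route. The device and phone criteria are listed as exclusions for the intervention as well as for observation. Someone who completes observation and then fails one of them can be counted as not eligible, and so already inside the 50%. This part of the objection stands: only people who leave before completing are clearly uncovered.

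The 50% may also be cautious. The Background reports that fewer than 30% reached 90% adherence in an earlier Ugandan sample aged 15–22. If 70% were eligible, 1256 completers would give 1256 × 0.70 = 879, and starters could lose about 29% (1 − 628/879) before falling below 628. That softens the practical risk. But the article does not present the 50% as an allowance for early loss, so possible slack there does not correct the derivation.

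Finally, 640 is larger than 628 and is no evidence of a shortfall. It is a separate inconsistency.

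**Conclusion.** The point holds as a mislabelled sample-size figure. On its stated denominator, 1256 is the number who must complete observation, and using it as the number to enrol assumes no loss over about 3 months. If loss follows the article's own annual attrition, the shortfall is 10 to 16 of 628 randomised. If it is 5% or 10%, the shortfall is 31 or 63, and 531 or 503 remain at the end against 560.

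These sizes rest on an assumed loss rate, on the 50% being accurate, and on enrolment ending at 1256. The consequence for power is modest, and the stated month-24 detectable difference is not overturned. The conflict between 628 and 640 needs no assumption.

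**What to change.** Choose one of two wordings in Sampling and participants. Either say that 1256 is the number who must complete observation with usable device data, and give starters as 1256 / (1 − assumed loss) with the assumed loss stated. Or say that the 50% is a share of those enrolled and already includes people who leave during observation, if the earlier data at the site support that.

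Make 628 randomised the recruitment target. If 1256 enrolled is a cap, restate the expected randomised number and the detectable differences that go with it.

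Use one randomised total throughout: bring the 640 in Limitations into line with 628, or explain it.

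The cost is wording only if the target is 628 randomised, apart from any extra clients enrolled to reach it. The article already allows extra recruitment time and reports that recruitment is still under way. Under a cap, the cost is a slightly less favourable stated figure.

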#### Exclusion criteria

Exclusion criteria for the 3-month observation period preceding the GOALS intervention and for the GOALS intervention:Is not willing or able to use the Wisepill device when taking ART medicationHas mental health problems that require immediate treatment (e.g., psychotic symptoms), a diagnosed mental disorder that would limit the ability to participate (e.g., dementia), or cognitive impairments that result in a limited ability to provide informed consent.No longer has access to a phone (less than 5 out of 7 days), if phone access changed over the course of the 3-month observation periodParticipating in another studyUnable to read

### Randomization

Random treatment assignment will occur after participants are recruited, and before they complete a baseline survey using a 1:1:1:1 ratio. Randomization will be done using sequential assignment while stratifying by baseline adherence measured during the observation period (0–54%, 55–71%, 72–82%, 83–89%). Stratification will be performed to increase power and achieve better balance than in a simple random draw. A randomization schedule will be established ex ante and sequential participants within a stratum randomized accordingly. The randomization schedule will contain blocks of four possible randomizations to the three treatment arms or the control group, with the order of the four possibilities randomized each time a new block begins. We will use the *ralloc* function in Stata 17 to generate the randomization lists, which will be uploaded to SurveyCTO and programmed to randomize participants on the spot.

The observation phase lasts approximately 3 months, after which adherence-based eligibility is determined, and all recruited participants will complete a baseline survey. They will be informed of their assignment to either one of the three intervention arms or the control group *after* completing the baseline survey. Participants who provide informed consent will be asked to participate in the baseline survey *before* the treatment assignment is revealed to make sure group assignment does not influence the answers given.

Participants cannot be blinded to their treatment status and neither can interviewers. The data analyst who will conduct the impact analysis will be blinded to treatment assignment.

As the only blinded party is the analyst, and the blinding occurs to avoid any bias of the analyst to find a statistically significant effect for the intervention group(s), we cannot think of a justified reason for unblinding the analyst.

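### Fixed blocks of four at one open-label site make up to a quarter of allocations deducible, just after a judgement-based device-use exclusion

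*Protocol article*

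**What the plan says.** **Sequence.** Under Randomization, participants are stratified by observed adherence (0–54%, 55–71%, 72–82%, 83–89%), and "A randomization schedule will be established ex ante and sequential participants within a stratum randomized accordingly". On the blocks: "The randomization schedule will contain blocks of four possible randomizations to the three treatment arms or the control group". Only the sequence inside a block changes from one block to the next: "with the order of the four possibilities randomized each time a new block begins". Block length is therefore constant, with one slot per arm.

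**Draw and reveal.** The lists are generated in Stata, "which will be uploaded to SurveyCTO and programmed to randomize participants on the spot". On timing: "Random treatment assignment will occur after participants are recruited, and before they complete a baseline survey". The same section says the arm is disclosed only once that survey is complete. It also says that participants and interviewers cannot be blinded, and that the analyst is the only blinded party.

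**Exclusion before randomization.** Wisepill procedures, on low recorded adherence in the 3-month run-in: "Participants who are unable to use the device consistently will be excluded from the study after careful discussion of the reason for the low observed" [...]. A parenthesis gives the purpose of that discussion, which is not to lose clients whose adherence is truly low. The Exclusion criteria apply the device criterion to the intervention phase as well as to the observation period.

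**Who is on site.** The trial takes place at one clinic (Study sites; Limitations). Under Data management, a Uganda team of six (one leader, two lead interviewers, three supporting members) collects all data and delivers the in-person intervention. Under Study design, the coordinator measures baseline adherence in order to set the assigned subgoals.

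**The concern.** Concealment fails if a person who influences entry can work out the arm the next client would receive. Three stated features combine here. The blocks are short and of constant size. Arms become known to site staff once revealed. A discretionary exclusion comes immediately before the draw.

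Because slots are used in order within a stratum, a client excluded before the draw consumes no slot, and the next eligible client in that stratum takes it. Someone who had deduced the coming arm could therefore, knowingly or not, lean towards keeping or dropping a borderline client.

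The endpoint makes this relevant. The primary outcome is adherence recorded by Wisepill, so a client who takes pills without using the device counts as non-adherent. Uneven retention of such clients would move the arm means. Stratification would not correct this, because the selection would act within a stratum. Intention-to-treat analysis would not either, because excluded clients never enter the randomized set.

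**Working it through.** **Inputs.** Block size 4 with one slot per arm, and four strata (Randomization). Randomized sample 628 (Sampling and participants).

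**The article's own figure.** 560 × 1.06² = 629.2, reduced to 628 = 4 × 157. This reproduces and serves here only to count blocks.

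**Guessing under fixed blocks of four.** Take an observer who knows the arms already revealed in the current block. The chance of naming the next arm is 1/4, 1/3, 1/2 and 1 for slots one to four.

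- Mean hit rate: (1/4 + 1/3 + 1/2 + 1)/4 = 2.083/4 = 52.1%, against 25% with full concealment.
- Known with certainty: one slot in four, or 25%. As a count, at most 628/4 = 157; unfinished blocks (up to one per stratum) lower this slightly.

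**Control versus any incentive arm.** The next client is surely in an incentive arm when control has already appeared in the block: (0 + 1/4 + 2/4 + 3/4)/4 = 37.5%. The next client is surely in control only at slot four with control unused: 1/4 × 1/4 = 6.25%. Together, 43.75%.

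**How many clients this could touch.** The 157 spans all strata. A client at 83–89% is an unlikely case of inability to use the device. If the strata were of equal size (an assumption), the lowest would hold about 628/4 = 157 clients and about 157/4 ≈ 39 certain allocations. Only those with a borderline device judgement matter, and the article gives no figure for them, so a bias in adherence cannot be computed.

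**Varying block sizes.** Simulated with 157 clients per stratum and 200 runs, sizes drawn with equal probability. The observer guesses optimally and knows the set of sizes but not their order.

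| Block sizes | Best-guess hit rate | Known with certainty |
|---|---|---|
| 4 (fixed) | 51.9% | 24.8% |
| 4, 8 | 48.6% | 7.3% |
| 4, 8, 12 | 46.1% | 3.6% |

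The first row agrees with the exact values, apart from simulation error and the unfinished last block. An observer who did not know the set of sizes could do no better than the other two rows.

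**The case against.** The strongest reply is that the deduction needs more than the article shows anyone to have. Wisepill procedures names no one as deciding the device exclusion. The trackers under Strategies to improve adherence to intervention protocols count people randomized to each group, and are not described as showing order or stratum. Four separate sequences would have to be followed without error. SurveyCTO, not staff, makes the draw, and the reveal is held back until after the survey. The exclusion follows three months of monitoring and carries a stated guard against dropping truly low adherers.

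Much of this stands. It makes 52% and 25% ceilings, and it confines the risk to a small set of clients. It does not remove the risk. The block size is printed in the article, the coordinator knows each client's baseline adherence and hence the stratum, and no blinded party other than the analyst is described. The delayed reveal protects survey answers, not the entry decision. The guard states an aim.

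A reader might also infer that drawing the arm before the baseline survey is itself a fault, or that the lack of a numeric device-use threshold is one. Neither follows. A hidden draw is not a route to selection, and a condensed article may leave such a threshold to the full protocol.

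**Conclusion.** The point holds as a risk to allocation concealment. With perfect tracking by stratum, up to 25% of allocations are certain in advance, and the best-guess rate is at most 52% against 25% by chance.

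Stronger readings are tempting and unsupported. The documents do not show that staff can always foresee the arm: outside the last slot, naming the specific arm is only a better-than-chance guess. They do not show that 157 clients are exposed to selection, since that figure counts certain slots in every stratum. They do not show that any selection took place.

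The conclusion assumes that someone with influence on the device exclusion follows revealed arms by stratum. That is feasible for a small team at one clinic, but the article does not state it. The change is worth making because it costs little.

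**What to change.** **Block sizes.** In Randomization, for allocations still to be made, replace the fixed blocks of four with randomly varying sizes within stratum, for example 4, 8 and 12. Keep the sizes out of anything site staff can read while enrolment continues. This removes most certain predictions (25% to about 4%) but less of the guessing (52% to about 46%).

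**Order of entry.** In Randomization and Wisepill procedures, require all eligibility and exclusion decisions, including device use, to be recorded and locked in SurveyCTO before it draws the assignment. This prevents exclusions after the draw and leaves an audit trail. It does not by itself prevent guessing, because a deduction from earlier reveals can precede the lock. The two changes therefore belong together.

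**Cost.** A regenerated list and a reordered form, with no change to arms, sample size or the strata terms in the models. Within a stratum, one arm can lead another by at most one client in a block of four, and by at most three in a block of 12 (12/4 = 3 slots per arm), so slightly more imbalance is possible. Recruitment was already under way at the May 2023 protocol date (Trial status), so only the remaining allocations benefit.
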